## Abstract

**Highlights:**

**What are the main findings?**
This protocol describes a four-arm additive randomized controlled trial evaluating a multidisciplinary intervention combining power-based multicomponent training, pelvic floor muscle activation instructions, and psychoeducation in older women with urinary incontinence.The study will assess the additive effects of progressively combining pelvic floor muscle activation instructions and psychoeducation with power-based multicomponent training.

**What are the implications of the main findings?**
Findings may support the implementation of multidimensional interventions targeting both urinary incontinence, balance and fear of falling in community-dwelling older women.The trial may contribute to the development of more comprehensive and integrated geriatric rehabilitation strategies.

**Abstract:**

**Background/Objectives**: Urinary incontinence (UI) and impaired balance are common geriatric syndromes that negatively affect health and quality of life in older women. However, the combined effects of power-based multicomponent training (PMT), pelvic floor muscle (PFM) activation instructions, and psychoeducational (PSY) support remain unclear. This study aims to evaluate the effects of a PMT, alone or progressively combined with PFM activation instructions and PSY support, on PFM function, UI symptoms, balance, fear of falling, and physical function in community-dwelling older women. **Methods**: This study describes the protocol for an 18-week, four-arm additive, parallel-group, assessor- and analyst-blinded randomized controlled trial with a 6-month follow-up. A total of 120 women aged 60–80 years with UI will be randomly assigned to four groups: (1) PMT only (EX), (2) PMT plus verbal PFM activation instructions (EXVERB), (3) PMT combined with PFM activation instructions and psychoeducational sessions (EXVERBPSY), or (4) a control group receiving educational sessions on geriatric syndrome prevention. Sessions will be conducted twice weekly for 18 weeks. The single primary endpoint is maximal PFM strength assessed by the manometric perineometry. Pre-specified secondary outcomes include additional PFM function measures, upper- and lower-limb (LL) strength and power, balance performance, fear of falling, quality of life, psychological well-being, and anthropometric variables. Assessments will be conducted at baseline, post-intervention, and 6-month follow-up. The trial is registered at ClinicalTrials.gov (NCT06839040). **Expected results**: This trial is expected to provide evidence on the effectiveness of a multidisciplinary intervention combining exercise, PFM activation strategies, and PSY support for reducing UI severity and improving balance performance and fear of falling in older women. **Conclusions**: This protocol describes a four-arm additive randomized controlled trial evaluating a multidisciplinary intervention targeting two highly prevalent and interrelated geriatric syndromes. The study may contribute to the development of more comprehensive exercise-based and PSY interventions for older women and may inform healthcare strategies aimed at promoting healthy ageing and improving the management of UI and fear of falling.

## 1. Introduction

The global aging population has led to a substantial increase in the prevalence of geriatric syndromes, particularly among women [1]. Age-related anatomical and functional changes contribute to impairments in postural control and neuromuscular function, increasing the risk of falls and urinary incontinence (UI) [2]. Fear of falling is highly prevalent among community-dwelling older adults and is strongly associated with the history of previous falls. Falls are a major public health concern and remain one of the leading causes of injury-related morbidity and mortality worldwide, prompting the development of international fall-prevention strategies [3,4].

UI is especially common in older women and is associated with significant psychological, social, and economic consequences [5]. Conservative interventions, particularly pelvic floor muscle (PFM) training, are recommended as first-line treatment and supported by high-quality evidence. Beyond its direct impact, growing evidence highlights a close relationship between UI and fall risk. Women with UI present a markedly higher likelihood of falling, which has been attributed to both intrinsic factors, such as reduced muscle strength and impaired postural control, and extrinsic factors related to functional limitations [6,7].

Biomechanical and neuromuscular studies have demonstrated an interaction between the PFM and key trunk and lower-limb (LL) muscles, including the transversus abdominis, gluteus maximus, and paraspinal musculature, underscoring the role of lumbopelvic stability in balance control [8]. Greater severity of UI has been associated with poorer balance performance and reduced postural stability in older women, particularly in those with diminished PFM strength. Consequently, international clinical guidelines increasingly recognize UI as a relevant component of multifactorial fall-risk assessment, reinforcing the need to address both conditions concurrently [9,10].

Although isolated PFM training remains the gold-standard intervention for UI, there is growing interest in complementary or more accessible strategies that may enhance functional outcomes and long-term adherence in older adults. General physical exercise has demonstrated beneficial effects on physical function and has been shown to contribute to the prevention and management of both UI and fear of falling [11,12,13,14]. In this context, multicomponent training programs (MTP), which combine strength, balance, mobility, and functional exercises within integrated sessions, are widely recommended to counteract age-related functional decline and reduce fall risk [15,16].

Within this framework, power-based MTP (PMT) represents a specific approach that emphasizes high-velocity force production to enhance functional performance [17]. In older adults, muscle power declines earlier and more rapidly than maximal strength and plays a critical role in tasks such as balance recovery and mobility. Power-oriented exercises have therefore been identified as particularly effective for improving functional capacity and fall-related outcomes in aging populations [18,19].

In addition to physical interventions, educational and PSY approaches may further enhance treatment effectiveness by addressing psychological barriers such as fear of falling, embarrassment, and low self-efficacy. These factors negatively influence physical activity participation and adherence, especially among older women with UI. Integrating PSY support within exercise-based interventions may promote behavioral change, improve adherence, and optimize functional outcomes [11,20].

The PSY component targets three interrelated psychological mechanisms expected to enhance intervention effects on the clinical outcomes. First, emotion regulation and acceptance-based strategies [21,22] address the shame, social anxiety, and experiential avoidance associated with UI, and the hypervigilance and activity curtailment driven by fear of falling, thereby facilitating sustained participation in the exercise programme [5,20,23]. Second, self-compassion training [24] reduces the negative self-evaluative responses triggered by UI episode, including self-criticism and feelings of loss of control—which amplify UI impact beyond its objective severity and are associated with poorer quality of life and reduced treatment engagement. Third, enhancement of self-efficacy for exercise adherence and UI self-management addresses a well-established mediator of treatment outcomes in older adults [25], given that UI-specific self-efficacy has been associated with greater adherence to PFM training and superior functional outcomes in comparable populations.

Although MTP and educational interventions have shown positive effects independently, existing studies have largely examined physical and psychosocial strategies in isolation [11,20,26]. This fragmented approach highlights the need for integrative, multidisciplinary interventions capable of simultaneously addressing UI, fall risk, and related psychological factors. Previous studies combining resistance exercise with PFM training have shown promising improvements in UI outcomes, supporting the integration of whole-body exercise and targeted PFM interventions [7]. Combining PMT with targeted PFM activation may optimize both LL function and PFM function, while PSY support may further enhance adherence, self-efficacy, and long-term behavioral change.

Beyond its established role in fall prevention, PMT may contribute to UI symptom reduction through four complementary mechanisms: (1) reflexive co-activation of PFM during closed kinetic chain resistance exercise [27,28]; (2) improvement of functional continence through gains in lower-limb power, walking speed, and sit-to-stand performance, which reduce UI episodes attributable to functional mobility limitations [7,29]; (3) improvement of body composition and reduction in intraabdominal pressure, a recognised risk factor for stress and mixed UI [17,30]; and (4) enhancement of lumbopelvic neuromuscular coordination between the transversus abdominis and pelvic floor, which constitutes a recognised mechanism of stress UI during physical effort [31,32]. These mechanisms provide an evidence-based rationale for combining PMT with targeted PFM activation instructions and psychoeducational support in a multidisciplinary intervention for UI in older women. Together, these complementary components are expected to provide greater overall benefits than each intervention delivered in isolation. To date, evidence evaluating combined models that integrate PMT, targeted PFM activation, and PSY support remains limited [7,15,16,20].

Beyond their clinical consequences, UI and fear of falling generate a substantial burden on healthcare systems due to their high prevalence, associated healthcare resource utilization, functional decline, and economic costs [3,4,5]. Therefore, evaluating integrated intervention models in community-dwelling older women is aligned with current healthcare priorities aimed at promoting prevention, patient-centred care, healthy ageing, and sustainable healthcare delivery. Given the substantially higher prevalence of UI among older women and the important contribution of female-specific anatomical and physiological factors, such as pregnancy, childbirth, and menopause, the present trial focuses exclusively on women. Restricting the study population to older women also provides a more homogeneous sample, reducing clinical heterogeneity associated with sex-specific mechanisms of UI and facilitating interpretation of the intervention effects. This study protocol aims to evaluate the effects of three combined intervention strategies over an 18-week period on PFM strength, LL function, balance, and UI symptoms in community-dwelling older women, as well as the maintenance of these effects at 6-month follow-up.

Based on the four-arm additive randomized controlled trial design and the multidimensional scope of the intervention, the following hypotheses are proposed:

**H1.** 
*Older women receiving the most comprehensive intervention (EXVERBPSY) consisting of PMT combined with PFM activation instructions and PSY, will demonstrate greater improvements in PFM function, LL strength/power, balance and UI symptoms compared with the control group and groups receiving partial interventions.*

**H2.** 
*All intervention groups will demonstrate progressively greater improvements than the control group, consistent with the additive contribution of each intervention component, with the greatest benefits expected in the EXVERBPSY group.*

**H3.** 
*Improvements observed immediately post-intervention will be partially maintained at 6-month follow-up, with greater long-term retention observed in the EXVERBPSY group.*

**H4.** 
*Among participants in the intervention groups, greater residualised improvements in psychological well-being (SF-36 Mental Component Summary score) and fear-of-falling-related self-efficacy (FES-I Short) from T0 to T1 will be positively associated with higher intervention adherence and with greater residualised improvements in the primary endpoint (maximal voluntary contraction pressure assessed by manometric perineometry) and the prespecified secondary outcomes at T1 and T2.*

## 2. Materials and Methods

### 2.1. Study Design

This study is designed as a four-arm additive, parallel-group, assessor- and analyst-blinded randomized controlled trial to evaluate the incremental contribution of PFM activation instructions and PSY when added to a PMT. The intervention will be conducted over an 18-week period, followed by a 6-month follow-up. The primary aim is to examine the combined effects of three intervention strategies on PFM function, LL performance, and balance in community-dwelling older women with UI.

Participants will be randomly allocated to one of four parallel groups: (1) a power-oriented PMT (EX); (2) exercise combined with verbal instructions to facilitate PFM activation during exercise (EXVERB); (3) exercise combined with PFM activation instructions and PSY support (EXVERBPSY); or (4) control group receiving educational sessions.

The intervention will be delivered over 18 weeks, with supervised sessions conducted twice weekly (55–60 min per session). Outcome assessments will be collected at baseline, immediately post-intervention (week 18), and at the 6-month follow-up to evaluate the persistence of effects. Data collection is planned from January 2026 to January 2027.

This study protocol has been prepared and is reported in accordance with the SPIRIT 2025 Statement (Standard Protocol Items: Recommendations for Interventional Trials) [33]. The results of the completed trial will be reported in accordance with the CONSORT 2025 Statement (Consolidated Standards of Reporting Trials) [34]. Analyses will follow the intention-to-treat principle. Ethical approval has been granted by the Ethics Committee of the Catholic University of Valencia (ID: UCV/2022-2023/123). The study is registered at ClinicalTrials.gov (Identifier: NCT06839040) and will be conducted in accordance with the Declaration of Helsinki.

The schedule of enrolment, interventions, and assessments, following the SPIRIT 2025 Statement, is presented in Supplementary Material Table S1.

### 2.2. Study Population

The study sample will include community-dwelling older women aged 60 to 80 years with a clinical diagnosis of UI. The International Consultation on Incontinence Questionnaire—Short Form (ICIQ-SF) [35] will be used to quantify UI symptom severity and impact at baseline and follow-up assessments. UI subtype (stress, urgency, or mixed) will be classified by a specialized physiotherapist according to the diagnostic criteria proposed by the International Continence Society (ICS) [36], based on participant’s medical history, symptom profile, and standardized clinical assessment prior to randomization. Cognitive function will be routinely assessed using the Mini Mental State Examination (MMSE). The Global Deterioration Scale (GDS) will only be used when administration of the MMSE is not feasible or considered inappropriate. When both instruments are available, the MMSE result will determine eligibility. Participants will be recruited from the Nau Gran program at the University of Valencia (Spain) and public centers affiliated with the City Council of Manises (Spain).

#### Selection Criteria

Detailed inclusion and exclusion criteria are presented in Table 1.

### 2.3. Recruitment Process and Screening

Participants will be recruited through informational sessions, posters, and community outreach activities conducted in collaboration with the Nau Gran program at the University of Valencia and public centers affiliated with the City Council of Manises. Interested individuals will be invited to attend an initial screening visit, during which the study objectives, procedures, potential risks, and benefits will be explained in detail.

The screening process will include demographic data collection, assessment of UI symptoms severity using the ICIQ-SF, cognitive screening using the GDS or MMSE, as appropriate, and a brief health history interview to verify inclusion and exclusion criteria, including the presence of a clinical diagnosis of UI. Only participants meeting all inclusion criteria will be enrolled and randomized. Written informed consent will be obtained prior to enrollment, and participants may withdraw at any time.

### 2.4. Sample Size Calculation

Sample size was estimated a priori using G*Power 3.1 [37]. Maximal voluntary contraction pressure (mmHg), assessed by manometric perineometry, was selected as the single primary outcome because it provides an objective and quantitative measure of PFM strength and is the outcome most directly related to the primary study hypothesis.

Previous randomized controlled trials involving women with UI have shown that vaginal manometric measures of PFM strength and endurance are responsive to exercise-based interventions incorporating specific or voluntary PFM contractions. In particular, Gonzaga et al. [38] reported improvements in manometric measures of PFM strength and endurance following PFM training and Pilates exercise performed with voluntary PFM contraction in postmenopausal women with UI. However, because previous studies are characterized by relatively small sample sizes and heterogeneous interventions and do not provide either a directly applicable standardized effect size or an established clinically important difference for the planned group-by-time comparison, Cohen’s f = 0.24 was selected as a conservative a priori planning assumption rather than an empirically derived effect estimate [39,40].

The calculation was based on a repeated-measures ANOVA model (within-between interaction; four groups; three time points: T0, T1, T2; two-tailed α = 0.05; statistical power = 1 − β = 0.80; assumed correlation among repeated measures r = 0.50; and Cohen’s f = 0.24). Under these assumptions, the minimum analytical sample required was estimated at 96 participants. Nevertheless, the planned recruitment target was set at 120 participants (30 per group). This target exceeds the minimum sample size required by the formal power calculation and was selected to preserve balanced allocation across the four intervention groups, accommodate anticipated attrition and incomplete follow-up data, and improve the precision and stability of the estimated longitudinal treatment effects obtained from the planned linear mixed-effects models (LMM). The anticipated attrition rate was conservatively estimated at 20%, based on participant retention reported in comparable randomized exercise-based interventions involving older women with UI [7,41,42].

The primary analysis will be performed using LMM framework consistent with the longitudinal design described in the Statistical Analysis Section 2.8. Although the analytical model differs from the repeated-measures ANOVA framework in G*Power 3.1, the latter was used to provide a transparent and reproducible a priori approximation of the required sample size under a balanced design and the stated correlation assumptions. Any difference in statistical power between this approximation and the final LMM is acknowledged as a limitation of the sample size estimation [43].

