### Limitations

The present protocol has several limitations that should be acknowledged.

(i)The active intervention groups receive substantially more participant–therapist contact than the educational control group (36 supervised exercise sessions vs. four monthly educational sessions), which may contribute to observed between-group differences beyond the specific intervention components. The control condition was intentionally designed to reflect realistic community practice rather than an attention-matched control, and the educational sessions provided to this group, covering healthy ageing, fall prevention, and pelvic floor health, may have improved participants’ knowledge and health-related behaviours, potentially affecting some outcomes, although they were not expected to produce the specific physiological adaptations associated with supervised exercise.(ii)The sample size was calculated exclusively based on the primary endpoint (maximal voluntary contraction pressure assessed by manometric perineometry). Accordingly, this trial may not be adequately powered to detect smaller between-group differences in secondary outcomes or in the pre-specified subgroup analyses according to UI subtype. These analyses should therefore be considered exploratory and hypothesis-generating.(iii)The study is restricted to community-dwelling older women, limiting generalizability to institutionalised populations or men.(iv)Intracavitary EMG amplitudes will be normalised to within-session MVC (%MVC) to reduce inter-session variability; however, this approach does not fully eliminate variability arising from training-induced changes in MVC neuromuscular characteristics, and longitudinal iEMG findings should be interpreted with appropriate caution.(v)Movement velocity during power training sessions will not be directly monitored; although the maximum intended velocity instruction and RPE-based intensity targets provide operational control of the training stimulus, confirmation that participants trained within the intended velocity range on a repetition-by-repetition basis is not possible.(vi)Falls and near-falls will not be prospectively recorded during the intervention or follow-up period; future trials in this population should be adequately powered to include fall incidence as a primary endpoint alongside functional and psychological outcomes.(vii)The a priori sample size was estimated using a repeated-measures ANOVA approximation in G*Power 3.1 [43], as dedicated LMM-specific power calculators are not readily available; under the assumed compound-symmetry covariance structure this approximation is considered conservative and reproducible, but represents a minor methodological limitation of the a priori calculation.

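### The minimum of 96 participants for 80% power does not follow from the G*Power inputs listed in section 2.4

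*Protocol article*

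**What the plan says.** Section 2.4 sizes the trial on the primary endpoint, maximal voluntary contraction pressure, with a "repeated-measures ANOVA model (within-between interaction; four groups; three time points: T0, T1, T2". It adds "two-tailed α = 0.05", "statistical power = 1 − β = 0.80", "assumed correlation among repeated measures r = 0.50" and Cohen's f = 0.24, which it describes as a cautious planning assumption and not an empirical estimate. It then states: "Under these assumptions, the minimum analytical sample required was estimated at 96 participants". The recruitment target is 120 (30 per group), with attrition put at 20%.

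The same section says of the ANOVA framework that "the latter was used to provide a transparent and reproducible a priori approximation of the required sample size". Limitations item (vii) assumes compound symmetry and says "this approximation is considered conservative and reproducible". The only shortfall conceded in either place is that the analysis will use a linear mixed model while the calculation used repeated-measures ANOVA.

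Section 2.8.1 places the primary inferential interest on the group-by-time interaction. Five pairwise contrasts, Holm-corrected at each time point, follow if that interaction is significant.

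**The concern.** Every input that G*Power asks for is given, except the effect-size option and the nonsphericity correction epsilon. A reader can therefore repeat the calculation, and the article says that it can be repeated. When it is, 96 does not appear under any of the three effect-size options.

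This figure carries the trial's power claim for its single primary endpoint, and the target of 120 is built on it. Without the option, a reader cannot tell whether 96 analysable women give far more than 80% power or clearly less. The concession about ANOVA versus mixed model does not cover this, because the ANOVA calculation fails on its own inputs.

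**Working it through.** **Inputs.** From section 2.4: k = 4 groups, m = 3 times, f = 0.24 (f² = 0.0576), r = 0.50, alpha = 0.05, power = 0.80. Epsilon is not stated. I take 1, which the compound symmetry in Limitations (vii) implies.

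**Test.** The interaction F test has df1 = (k − 1)(m − 1) = 3 × 2 = 6 and df2 = (N − k)(m − 1) = 2(N − 4). Power is the upper tail of a noncentral F beyond the 5% critical value. The noncentrality λ depends on the effect-size option:

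- default: λ = f² × N × m/(1 − r) = 0.0576 × N × 6
- as in Cohen: λ = f² × N × (m − 1) = 0.0576 × N × 2 (r is not used)
- as in SPSS: λ = f² × (N − k) × (m − 1) = 0.0576 × (N − 4) × 2 (r is not used)

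**Attempt to reproduce 96.**

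| Option | Smallest N for 80% | With equal arms | λ and power at N = 96 | λ and power at N = 120 |
|---|---|---|---|---|
| Default | 43 (0.803) | 44 (0.815) | 33.18; 0.996 | 41.47; 0.9996 |
| As in Cohen | 122 (0.802) | 124 (0.810) | 11.06; 0.679 | 13.82; 0.794 |
| As in SPSS | 126 (0.803) | 128 (0.810) | 10.60; 0.656 | 13.36; 0.778 |

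None gives 96. A simulation of the repeated-measures interaction test on the default scale agrees: power is 0.81 at 44 and 0.997 at 96.

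**Could an unstated setting explain it?** On the default scale, epsilon 0.75 gives 52 and epsilon 0.5 gives 68. An approximate MANOVA version gives about 43. Changing stated inputs does not help either: two time points give 52, and r = 0 with three time points gives 84.

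**What would make 96 right?** On the default scale, 80% power at N = 96 needs f of about 0.156: λ = 0.1564² × 96 × 6 = 14.09, power 0.80. On the other scales it needs f of about 0.271 (Cohen) or 0.277 (SPSS).

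**How far apart the scales are.** Equating the default and as-in-Cohen noncentralities, a default f of 0.24 corresponds to an as-in-Cohen f² of 0.0576 × 3/(2 × 0.5) = 0.1728, so f = 0.416. Whether 0.24 is a cautious value therefore cannot be judged until the scale is named.

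**Attrition step.** 96/(1 − 0.20) = 120. This step is correct; only its starting figure is unsupported.

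**Pairwise contrasts (secondary).** The article gives no SD and no difference in mmHg, so this is in SD units. I assume a baseline-adjusted comparison with r = 0.5, which multiplies the variance by 1 − 0.5² = 0.75, and a two-sample noncentral t with 2n − 2 df. The strictest Holm step is 0.05/5 = 0.01. The differences detectable with 80% power are:

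| Per arm | alpha 0.05 | alpha 0.01 |
|---|---|---|
| 24 | 0.72 SD | 0.89 SD |
| 30 | 0.64 SD | 0.79 SD |

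The level that applies to a given contrast lies between the two columns, depending on its place in the Holm order.

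**The case against.** The strongest reply is that the error is harmless. Section 2.4 lists r = 0.50, only the default option uses r, and on that reading both 96 and 120 exceed what is needed. No patient, procedure or analysis has to change. This stands, and it limits the consequence. It does not rescue the sentence, because a minimum stated under given assumptions should be the minimum those assumptions produce, and 44 is less than half of 96.

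A reader might go further and infer that the trial is underpowered. The documents do not support that. It would require that the authors chose an option that ignores an input they list. Even then, 120 women without loss would give 79% or 78%. Only the authors know which option was entered. How 96 arose is also unknown: it equals 80% of 120, but nothing in the article says it was worked back from the target.

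A reader might also infer that sizing on the omnibus test is itself an error, or that 80% power is claimed for the contrasts. Neither holds. Section 2.8.1 names the interaction as the primary inferential interest and tests the contrasts only after it is significant, and no power is claimed for them. What remains is a gap in clarity. H1 and the value of each added component are answered by the contrasts, while the power caveat in Limitations (ii) mentions only secondary outcomes and subgroups.

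**Conclusion.** The stated minimum of 96 is wrong as written. With epsilon = 1, the listed inputs require 44 on the natural (default) reading, 124 as in Cohen or 128 as in SPSS. Power at 96 is 99.6%, 68% or 66% respectively, not 80%. The direction of the error depends on an option that the article does not name, so the finding is that N, f and power are mutually inconsistent, and not that the trial is too small. The description of the calculation as reproducible is not met, and its description as conservative cannot be accepted until the scale of f is known.

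The pairwise point is a lower-priority addition. Its figures rest on the assumed r = 0.5 and on 24 analysable women per arm.

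**What to change.** In section 2.4, state the G*Power effect-size option and the epsilon actually entered, and correct whichever of N, f or power is inconsistent so that the three agree. The authors should take this from their own G*Power record and not choose an option afterwards to fit 96. Keep the target of 120. In section 2.4 and Limitations (vii), remove the claims that the calculation is reproducible and conservative unless the corrected version supports them.

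As a lower priority, add one sentence saying that the stated power applies to the omnibus group-by-time test only. It can add that 24 per arm (baseline-adjusted, assumed r = 0.5) detects about 0.72 SD at alpha 0.05 and about 0.89 SD at the strictest Holm step of 0.01 with 80% power.

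The cost is the rewording of one paragraph and one limitation item. No extra participants are needed and the analysis does not change. The stated power or the assumed effect size will read differently from now.
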